### Study design

The study consists of 2 parts: the registry set and the trial set. The two sets of this study share a common data pool, which contains all the enrolled patients. The registry set is designed as a multicentric, prospective, real-world registry (Research on Hybrid Operation Technique in the Treatment of Complex Brain Arteriovenous Malformations; ClinicalTrials.gov ID: NCT 03774017), and it occupies the whole data pool. The patients involved will receive traditional operation (TO) or one-staged hybrid operation (HO) and will be registered in the corresponding TO group or HO group. End points will be evaluated at scheduled time points. The safety and efficiency of the one-staged hybrid operation in treating complex bAVMs will be validated. The trial set is designed as a multicenter, prospective, pragmatic clinical trial (PCT). Patients in this set will be registered in the registry set in the meantime. PCT is a real-world modification of randomized clinical trial (RCT), consisting of an RCT part and a registry part. Patients have the right to choose the part in which they want to participate. The candidates in this set are patients harboring bAVMs with perforating arterial (PA) feeders. To them, an extra written informed consent is required. Patients who agree to take part in the RCT part will be randomly assigned to the HO or TO group and receive the corresponding treatment. Both of the sets share the same end points. The purpose of the trial set is to validate the benefits and risks of hybrid operation for lesions with perforating arterial feeders and the contribution of endovascular embolization. A strategy of multicenter stratified blocked randomization is used in the central randomization system (CRS), which is contained in Electrical Data Capture (EDC) system. When registering a participant in EDC system in the trial set, CRS generates an assignment result according to the demographic information. Each center is set as a stratifying level, which could reduce the differentiation of sample size between groups. The blind codes, generated by statistician, remain blind during randomizations to avoid potential selection bias. The design of this study is presented in Fig. 1. The grouping assignment is blinded to outcomes assessors. Both sets will be conducted between Jan 2016 and Dec 2020. The study is hosted by Beijing Tiantan Hospital, with the participation of 20 cooperation centers, including academic, military, and other public hospital (Table 1).

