### Sample size

#### Registry set

According to the relevant literature and data, the average morbidity rate of neural function deterioration is 38.6% [9–11, 34, 35]. The aim of the hybrid operation is to reduce the rate of neural function deterioration by 10%, referring to present studies [31–33]. To ensure the statistical power and the potency of exploring technical details, the sample size is set as the maximum operative capacity of participating centers. According to the records of the latest 5 years, the operative capacity of Beijing Tiantan Hospital is about 220 cases of bAVMs per year, and of other participating centers is 20 cases per year in total. A total of 1200 cases will be recruited into the cohort in the 5-year-recruitment. Among them, 800 cases will receive hybrid operations, and 400 cases will receive microsurgical operations.

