#### Trial set

Few studies have been found on bAVMs with perforating feeding arteries. Referring to relevant studies of bAVMs, the neural function deterioration rate was 38.6% in traditional operation and 19% in one-staged hybrid operation. By using PASS 14 (PASS Power Analysis and Sample Size software, NCSS, LLC, Utah, US) with a significance level of 0.05 and a statistical power of 0.9, the minimum sample size for each group is *n* = 117. In total, 236 patients will be enrolled in the trial set.

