### Statistical analyses

Statistical analyses will be conducted using the Statistical Package for the Social Sciences software (V.22.0; SPSS, Chicago, Illinois, USA). Demographic information (age, gender, race, provenance, occupation), medical histories (primary symptom, operation history, and past history, family history, smoking and drinking history), bAVM-related morphological and location features (eloquences and fiber tracks involved according to the task), angioarchitectural features (origin and type of feeding arteries, situation of nidus and draining veins), and admitting conditions (signs, mRS score and NIHSS score) will be cataloged into continuous or categorical variables and descriptively analyzed. The baseline conditions of cases involved in the two groups will be compared by the characteristics described above. The Chi-square test and Student t-test will be conducted between homogeneous cases of 2 groups in the outcome variables, including operation-related events (e.g., operative time, hemorrhagic volume, electrophysiological changes) and outcomes to make comparisons of their safety and efficiency in several aspects. Univariate and multivariate logistic regression analyses will be conducted to explore the correlations between the outcome index and variables above. Analyses of subgroups in the hybrid operation group will be performed to evaluate the contributions of different endovascular interventions. In the trial set, differences will be tested with Chi-square test. The effect of hybrid operation in the subgroup will be clarified.

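### The trial-set comparison uses only an unadjusted chi-square test, although the primary outcome depends on admission mRS: the test is valid, but it gives up some precision

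*Protocol article*

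**What the plan says.** **Test.** The only test that Statistical analyses assigns to the randomised patients is "In the trial set, differences will be tested with Chi-square test". The same section plans univariate and multivariate logistic regression on the baseline variables, which include admission mRS and NIHSS. That regression is exploratory and is not tied to the trial-set comparison.

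**Outcome.** Outcome evaluation defines the primary outcome as an increase in mRS to a value above 2 in the three months after surgery.

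**Baseline data.** Study participants and Statistical analyses both have mRS recorded at admission. Spetzler-Martin grade is known for everyone, because Inclusion criteria admits grades I to IV. It is not named among the baseline variables.

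**Randomisation.** Study design stratifies by centre: "Each center is set as a stratifying level, which could reduce the differentiation of sample size between groups". It also has the system use demographic information, but the protocol's list of demographic items contains neither mRS nor grade.

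**Size.** Sample size, Trial set assumes that "the neural function deterioration rate was 38.6% in traditional operation and 19% in one-staged hybrid operation", "with a significance level of 0.05 and a statistical power of 0.9". It concludes that "the minimum sample size for each group is *n* = 117" and that "In total, 236 patients will be enrolled in the trial set".

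**The concern.** The outcome definition ties risk to where the patient starts. Below mRS 2 the number of points needed for an event falls with each step in admission mRS, so some prognostic gradient is likely from the definition alone. Admission mRS is collected, but neither the allocation nor the test uses it.

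Two things follow. Variation between patients that could be explained stays in the error term. And a chance difference in admission mRS between the groups passes straight into the estimated risk difference. The article leaves little slack in the sample size, and its Strengths and limitations section stresses keeping to the trial-set minimum. Precision that needs no extra patients is therefore worth having.

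**Working it through.** **1. Points needed for an event.** The final mRS must be at least 3 and above the admission value: from 0, 3 points; from 1, 2 points; from 2 or above, 1 point.

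**2. The stated sample size.** Inputs from Sample size, Trial set: p1 = 0.386, p2 = 0.19, d = 0.196, alpha 0.05 (taken as two-sided), power 0.90.

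- Unpooled variance: n = (1.960 + 1.282)² × (0.386×0.614 + 0.19×0.81) / 0.196² = 106.9.
- With continuity correction: n = (106.9/4) × (1 + √(1 + 4/(106.9×0.196)))² = 116.9, so 117. This matches the article.
- The total of 236 is 2 × 118. Power of the uncorrected chi-square is 91.7% at 117 and 91.9% at 118 per group (normal approximation).

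**3. Validity and power under a general covariate.** Simulation with 4,000 runs per scenario and 236 patients, marginal rates 38.6% vs 19%. Assumptions: 216 patients at one centre and 20 spread over 19 others, blocks of 4 within centre, and one standard normal prognostic covariate. The adjusted analysis is a logistic regression on group and that covariate.

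| Covariate effect (log-odds per SD) | Centre SD (log-odds) | Chi-square power % | Adjusted power % | Gain (points) |
|---|---|---|---|---|
| 0 | 0 | 91.8 | 91.6 | -0.2 |
| 0.5 | 0.5 | 91.6 | 92.5 | 0.9 |
| 1.0 | 1.0 | 91.6 | 93.3 | 1.7 |
| 1.0 | 0.5 | 92.1 | 95.1 | 3.0 |
| 1.5 | 0.5 | 92.1 | 97.3 | 5.2 |

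The simulation error of each power is about √(0.92×0.08/4000) = 0.4 points. Under no treatment effect the chi-square rejected in 4.4-5.0% of runs. A centre-stratified Mantel-Haenszel test had 90.4-91.0% power, so adding centre alone gains nothing.

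**4. Power with admission mRS itself.** The document gives neither the mRS mix nor the risk at each level, so both are assumed, at 118 per group.

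- Strong gradient (control risks 10/22/45/62/70% for mRS 0 to 4): 93.1% unadjusted vs 96.1% adjusted (marginal rates 38.8% vs 18.9%). Two other assumed mixes gave 93.5% vs 96.4% and 95.0% vs 97.0%. The gain is 2 to 3 points.
- Risk flat from mRS 2 upward, which follows the outcome definition most closely: 92-93% vs 93-94%, a gain of about 1 to 2 points.
- Mild gradient: 92.0% vs 92.7% in one set of runs, and a difference of -0.5 to +0.2 points in another.

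**5. Chance imbalance.** Under the strong gradient, imbalance in admission mRS alone shifts the expected risk difference by more than 5 points in 6-9% of trials.

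**The case against.** The strongest reply is that nothing here is wrong. A chi-square after stratified randomisation is a valid test, it fits the two-proportion calculation behind the sample size, and its power is already above the planned 90%. Covariate adjustment is also something a condensed article may leave to a fuller plan. The first part stands in full, and it limits the point to efficiency. The second stands only in part, because the article does name the test for this comparison and names no covariate.

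A second fair reply is that the size of the gain rests on assumed gradients. That is so, and with a mild gradient the gain is close to nil.

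A reader might go further and infer that centre stratification is ineffective because about 92% of patients come from one hospital, and that the randomisation system should be changed. The documents do not support this:

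- The share is 220/(220 + 20) = 91.7%, from about 220 cases a year at the host and, for the rest, "of other participating centers is 20 cases per year in total". Those are operative capacities for all bAVMs. No centre split is given for the 236 trial-set patients.
- The stated purpose of the strata is balance in group size, and blocking at the host serves that.
- If the split did carry over, about 236 × 20/240 = 20 patients would come from the small centres and many of their blocks would stay unfilled. With blocks of 4 (assumed) the mean imbalance among them is about 2.8 patients. Even an imbalance of 6 (115 vs 121) leaves power at 91.85%, against 91.89% for 118 vs 118.
- If one centre dominates, leaving centre out of the test costs practically nothing.

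**Conclusion.** The point holds as a modest improvement to a stated method, not as an error. The named test ignores a recorded baseline value on which the outcome definition itself depends. At the design effect the loss is about 0-1 points of power if the gradient is mild and about 1-3 if it is moderate to strong. The most extreme scenario assumed gives 97.3 - 92.1 = 5.2 points. The estimate is also left exposed to chance imbalance in admission mRS. These sizes rest on assumed mRS mixes and gradients, because the article gives neither.

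It would be wrong to infer that the trial-set p-value is invalid or that the trial is underpowered at its design effect. The case rests on admission mRS and, secondarily, grade, and not on centre.

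**What to change.** Before unblinding, prespecify the trial-set primary analysis as a logistic regression of the primary outcome on randomised group, adjusted for admission mRS and Spetzler-Martin grade. Include centre as host vs all others pooled, only to reflect the stratified randomisation. State in advance how mRS enters; categories 0, 1, and 2 or above would follow the outcome definition. Report the standardised risk difference with 95% CI and keep the chi-square as a sensitivity analysis.

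The model is feasible: at the design rates about 118×0.386 + 118×0.19 = 68 events are expected, against a handful of coefficients.

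The cost is wording in the analysis plan and making sure that grade is captured as an analysis variable. The downside is a model-based rather than a raw primary estimate. No change to the randomisation system is needed.

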### Data management

All the data in this study will be sourced from experienced physicians and radiologists in 20 participating centers, and they will be prospectively collected by full-time clinical research coordinators (CRCs) using both paper documents and a web-based electronic data capture system (EDC system). SUN HEALTH (Beijing) Health Care Group, a third-party CRO, is contracted to render the services of quality control and data management. The study is supervised and administered by the Ministry of Science and Technology of China and the Beijing Municipal Science and Technology Commission, and it receives resource support from the China National Clinical Research Center for Neurological Diseases. Issues that occur in the cohort will be reported to oversight authorities and evaluated. All data are available only to participating centers while the study is being conducted and will become public once the study concludes. All of the processes of data collection, statistical analysis, study result interpretations and dissemination are under the direct supervision of the principal investigator. The final results will be disseminated via printed media in December 2020.

### Duration of study

The study was approved and authorized to launch in September 2016 and was specified to close in December 2020. The recruitment of participants began on 1st January 2016 in the pilot study that had been launched. Participants enrolled after 1st September 2016 were involved in this study.

## Discussion

The study is designed for a real-world exploration of the benefits and risks of one-staged hybrid operation in the treatment of complex bAVMs. As the interventional clinical study seldom represents an ideal experimental condition, the 2-set design could reduce the study’s compromise of clinical practice. The registry set achieves the coverage of the target population without affecting the normal clinical treatment. General benefits, risks, indications and key technologies could be drawn from it. The trial set focuses on a group of specific participants who would probably get the most benefits from one-staged HO. It could provide high-level evidence as an RCT. The combination of registry and PCT improves the statistical power and research quality of the study in a practical sample size.

With the study, advantages of one-staged hybrid operation will be tested in the treatment of complex brain arteriovenous malformations. Among a variety of therapeutic methods, neither microsurgery, nor endovascular intervention, nor stereotactic radiotherapy could independently meet the requirements of both cure and neural function protection. The multistaged utilization of technical combinations between endovascular embolization and microsurgical resection or stereotactic radiotherapy is available in some bAVMs. Meanwhile, risks exist in the interval period between the stages, especially after partial embolization or stereotactic radiotherapy. The one-staged hybrid operation could eliminate the lesion once and for all without any of those risks. Moreover, it meets the requirement of both cure and neural function protection. However, its benefits have been proposed theoretically with reference to limited attempts [31–33] and experience in cardiac surgery. No high-quality evidence has been acquired to support the proposal. This study is designed to make the comparison between the one-staged hybrid operation and the traditional microsurgical operation for its benefits and risks, as well as the indications. A spanning development of neurosurgical operation might be facilitated by the study, which means a higher cure rate and lower disability rate in patients with complex bAVMs.

### Strengths and limitations

This study, consisting of a prospective real-world registry and a pragmatic clinical trial, will help clarify whether one-staged hybrid operation is a safe and efficient alternative to traditional surgical operation in the treatment of complex bAVMs. It evaluates the effect of one-staged perforating arterial embolization on the surgical resection of complex AVMs. It will help explore indications, key technologies, and workflows of one-staged hybrid operation, as well. However, this study has limitations. Varieties of factors are related to the outcome of complex AVMs. The sample size needs to be enlarged, if further subgroup analyses are required to clarify the effects of factors in details. And there is lower limit of sample size in the trial set. It needs to be critically obeyed to maintain the evidence level of this set.

## Abbreviations

AEDs: Antiepileptic drugs
AKA: As known as
bAVMs: Brain arteriovenous malformations
CRAs: Clinical research associates
CRCs: Clinical research coordinators
CRO: Contract research organization
CT: Computed tomography
CTA: Computed tomographic angiography
Dicom: Digital imaging and communications in medicine
DSA: Digital subtraction angiography
EDC: Electronic data capture system
HO: Hybrid operation
MR: Magnetic resonance
mRS: Modified Rankin Scale
NIHSS: National Institute of Health Stroke Scale
PA: Perforating artery
PCT: Pragmatic clinical trial
RCT: Randomized clinical trial
TO: Traditional operation
